### Eligibility criteria

Participants will be recruited if (1) aged between 13 to 18 years, (2) diagnosed as ASD children based on DSM-V criteria [28], (3) malnutrition according to Body Mass Index (BMI) [29], (4) not taking any diet advice or supplement, and (5) willing to participate. On the other hand, participants will be excluded if- (1) respondents provided consent but dropped out within the first week of enrollment, (2) allergy to any gluten-free, casein-free (GFCF), Soya free diet, (3) severe behavioral problems according to Gilliam Autism Rating Scale (GARS-2) [30].

### Outcome measurements

#### Explanatory variables

*Socio-demographic information*. Socio-demographic information will be recorded as participants’ personal, demographics, and other disease-related information by a structured questionnaire prepared by the researcher.

*Diagnosis of ASD*. Screening of Autism spectrum disorder (ASD) children will be based on the planned diagnostic criteria of the DSM-5 [28] committee. ICD-10 and DSM-IV-TR criteria for ASD were significantly revised in DSM-5 [31]. In the DSM-5, four previous types of Autism in DSM-IV (Autistic disorder, Asperger syndrome, childhood disintegrative disorder and pervasive developmental disorder- not otherwise specified (PDD-NOS) was merged in an umbrella term Autism spectrum disorder (ASD). Also, the first diagnostic category of ASD indicates deficits in social communication and interaction. For an ASD diagnosis, all of the following symptoms must be present (1) impairments in socio-emotional engagement with another person, (2) problems in nonverbal behaviors during communication, (3) problems in making or continuing communication with others. The presence of two or more of the following symptoms associated with limited interest and repetitive behaviors is required for the second domain as (1) persistent or repetitive speech, movement, or holding an object, (2) adherence to routines, rituals of verbal or nonverbal behavior patterns, or excessive resistance to change, (3) abnormal fixated interests or intensity of focus, (4) more or less reactivity to sensory input, or (5) unusual interest in sensory aspects of the environment. According to the third category, symptoms must appear in infancy but may not completely develop until societal demands exceed capacity. The symptoms must interfere with daily functioning. Also, the diagnosing psychologist offers severity ratings as social communication, limited interests, and repetitive patterns of conduct, ranging from 1 to 3. The highest severity grade of 3, denotes that the domain is seriously impairing users [32]. This tool shows approximately 98.5% sensitivity and 92% of specificity to diagnose ASD [33].

#### Primary outcome variables

*Gilliam Autism Rating Scale (GARS-2)*. The second edition of the Gilliam Autism Rating Scale (GARS-2) will use to assess the behavioral status and overall status of ASD Adolescents. It is a behavioral screening tool for individuals with ASD between 3–22 years of age, based on DSM-IV (Diagnostic and Statistical manual of mental disorder) criteria for ASD. This scale comprises 42 items ranging from 0–126 scores, divided into 3 subscales (stereotyped behavior, communication, and social behavior) [30].

*Anthropometric measurements (AM)*. Anthropometric measurement (AM) will use to measure the nutritional status of the child. Because it is non-invasive and less expensive than other methods, anthropometry, and circumference of the arm, abdomen, and thigh (MUAC) have long been considered nutritional status determiners [34]. BMI [29] of the child and adolescent will be measured as another indicator of nutritional status. As edema and hydration have the potential to affect weight and BMI values, therefore these factors will consider during the determination of these parameters [35]. These parameters will be pictured on the chart to assess nutritional status.

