There have been several systematic reviews and meta-analyses [14–16] conducted on the nutrition of ASD children. There are different opinions on dietary interventions for ASD in Adolescents [12, 17, 18]. It is assumed that gluten-free and casein-free diets can minimize the symptoms of ASD, but there are controversial theories about the effectiveness of the gluten-free and casein-free (GFCF) diet [17]. According to certain studies, the GFCF diet can assist with symptoms such as stereotyped attitude, cognitive and social function, attention, interaction, and mood [18]. Many explanations have been proposed to explain how the GFCF diet improves the features of autism. Of all of these, the opioid excess hypothesis is the most widely accepted. Gluten and casein both affect the central nervous system via the leaky gut, but opioids escape via inflamed and thinning stomach in children with ASD [12].

Therapeutic interventions are multidisciplinary approaches [19] that, composed of balance [20], gait training [21], Therapeutic horse riding [22], motor training [23], strength training [24], aerobic exercise [25], and executive functional tasks [26]. It is hypothesized that structured dietary intervention adjunct with regular treatment approaches may have a greater benefit in children with ASD but no such research in Bangladesh has been held yet. It is important to determine the combined outcome of a structured diet (SD) and regular therapy (RT) for improving nutritional status and behavioral indices in the child and adolescents with malnutrition having Autism in Bangladesh.

The study objectives are to (1) determine the socio-demographics and anthropometric measures related to malnutrition for ASD in Bangladesh, (2) to elicit the within-group difference between structured diet (SD) with regular therapy (RT) or usual diet (UD) with regular therapy (RT) therapy on nutritional status and behavioral indices in post-test (3months) and follow-up (6months) compared to baseline, and (3) to find out the effectiveness among groups (SD with RT versus UD with RT) and observations (pretest to post-treatment, pretest to follow up, and post-test to follow up) comparison in the improvement of nutritional status and behavioral indices.

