Occupational therapy intervention includes sensory integration that includes the 10 key therapeutic strategies [42] in the fidelity tool, on the individual needs of each child as, (a) setting up the space to encourage interaction, (b) providing for physical security, (c) offering options for sensory input, (d) achieving and preserving appropriate arousal levels, (e) modifying activities to offer the ideal challenge, (f) assuring the success of activities, (g) providing direction for behavior self-regulation, (h) establishing a fun atmosphere, (I) choosing an activity together, and (j) encouraging therapeutic partnerships [43]. These 10 areas will be divided into 3 primary categories as (i) modifying the environment and giving sensory possibilities for the kid throughout the therapy session; (ii) encouraging adaptive responses and offering the ideal challenge; and (iii) building the therapist-child relationship [44]. Other interventions include gross motor function through exercise including pegboard games, dexterity drills, crossword puzzles, ball games, balance training, sensory integration exercises, and play therapy [45]. Moreover, community mobility or travel training [46], cognitive behavioral therapy [47, 48].

A structured diet (SD) will be designed by a nutritionist. Participants will provide with written instructions about the healthy, gluten-free, casein-free, soy-free diet and vitamin and mineral supplement [13]. The nutritionist will provide detailed advice. The diet plan will depend on age, nutritional status, and BMI. Other comorbid diseases and allergies of the child and adolescent to specific foods and physical activity levels will consider. The major guiding principles of the dietary plans will include, (1) Consuming enough fruit and vegetables, especially leafy greens (preferably whole fruit), (2) A sufficient amount and quality of protein, (3) A sufficient but moderate calorie intake, (4) Consuming fewer "junk" meals and substituting them with wholesome snacks, (5) A wholesome, gluten-free, casein-free, and soy-free diet (HGCSF) that includes foods like poultry, fish, and meat as well as fruits and vegetables, potatoes, rice, and baby rice cereal, and (6) Refrain from using synthetic flavors, colors, and preservatives. Moreover, Vitamin or mineral supplements will be prescribed with the consent of a General Physician. The dosage will be determined by the physician.

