### Data analysis

According to the nature of the data, SPSS version 23 for Windows will be used for analysis. The distribution of data will be performed using normality indicators and normality tests such as the Kolmogorov-Smirnov test, and the Shapiro-Wilk test. Descriptive analysis will be performed by mean and standard deviation for the continuous data, and frequency and percentage categorical data. The baseline compatibility, between-group post-test, and follow-up variations among the groups will be assessed using MANOVA or the Multivariate Kruskal-Wallis (MKW) test, depending on the nature of the data. Repeated measure or Friedman’s ANOVA Three measures will be analyzed within-group using an ANOVA, and additional post-hoc analyses will be performed using paired sample t-tests or Wilcoxon tests. We will perform the intention to treat the analysis process for the drop-out of cases taking more than one month of interventions. In the case of a post hoc Bonferroni adjustment, the level of significance P < .05 will be converted to P < .0125.

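### BMI and MUAC are primary outcomes at ages 13 to 18 with no age- and sex-standardised metric specified, and the planned within-arm tests cannot separate the diet from normal growth, mainly at follow-up

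*Protocol article*

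**What the plan says.** All references are to the protocol article.

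- **Outcomes.** Under Primary outcome variables, anthropometry is listed with GARS-2: "BMI [29] of the child and adolescent will be measured as another indicator of nutritional status". The other measure is described as "circumference of the arm, abdomen, and thigh (MUAC) have long been considered nutritional status determiners", so three circumferences share one label. Oedema and hydration are named as influences on weight and BMI; age and sex are not. The values are to be shown on a chart that is not identified.
- **Population.** Under Eligibility criteria: "Participants will be recruited if (1) aged between 13 to 18 years". The nutritional criterion is "malnutrition according to Body Mass Index (BMI", with a citation but no cut-off, reference population or direction.
- **Objectives.** The second objective in the Introduction is to "elicit the within-group difference between structured diet (SD) with regular therapy (RT" or usual diet with regular therapy, on nutritional status and behaviour, at post-test and follow-up against baseline. The third compares the arms.
- **Analysis.** Under Data analysis, "Three measures will be analyzed within-group using an ANOVA" or a Friedman test, followed by paired t or Wilcoxon tests, with 0.0125 as the Bonferroni-adjusted post hoc level. MANOVA or a multivariate Kruskal-Wallis test compares the arms. No covariates are named.
- **Timing.** Under Study procedure, the post-test is at 12 weeks and follow-up is 6 months after that, about 9 months from baseline.

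**The concern.** At 13 to 18 years BMI and arm circumference generally rise with age without any treatment, and the expected level depends on age and sex. A paired test within one arm asks only whether the mean changed. If raw values are analysed, nine months of growth enters that change in full, in both arms.

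At stake is how the within-arm results on a primary outcome are read. A significant rise in the structured-diet arm could be reported as better nutrition when it shows only that the participants are older. The same rise in the usual-diet arm could be credited to regular therapy. Because the direction of malnutrition is not stated, the article also does not say that a rise is the improvement sought.

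**Working it through.** **What the plan's own figure covers.** The only sample-size figure rests on GARS-2. With a difference of 0.25 × 4.7 = 1.175, SD 1.7, two-sided alpha 0.05 and 80% power, it reproduces: 33 per arm, 66 in total. It does not depend on BMI or MUAC, so this point leaves it unchanged.

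**Inputs from the article.** 35 per arm (Sample size); post-test at 12 weeks = 12/52 = 0.23 year; follow-up at about 9 months, taken as 0.75 year (exactly 12/52 + 0.5 = 0.73 year); post hoc level 0.0125.

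**Inputs assumed, because the article gives none.** Untreated BMI growth of 0.4 to 0.8 kg/m2 a year; SD of within-person change 0.8 to 1.2 kg/m2, the same at both visits; no treatment effect.

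**Formula.** Expected change d = rate × time. The paired t statistic is noncentral t with 34 degrees of freedom and noncentrality d × √35 / SD. The two-sided critical value is 2.03 at alpha 0.05 and 2.64 at 0.0125.

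**Follow-up (0.75 year), chance of a significant within-arm result from growth alone:**

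| Rate per year | SD of change | d | Noncentrality | alpha 0.05 | alpha 0.0125 |
|---|---|---|---|---|---|
| 0.4 | 1.2 | 0.30 | 1.48 | 30% | 14% |
| 0.6 | 1.0 | 0.45 | 2.66 | 73% | 52% |
| 0.8 | 0.8 | 0.60 | 4.44 | 99% | 96% |

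With 0.73 year in place of 0.75 the results at 0.05 are 29%, 71% and 99%, so the rounding does not matter.

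**Post-test (0.23 year), same assumptions:**

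| Rate per year | SD of change | d | alpha 0.05 | alpha 0.0125 |
|---|---|---|---|---|
| 0.4 | 1.2 | 0.09 | 7% | 2% |
| 0.6 | 1.0 | 0.14 | 13% | 4% |
| 0.8 | 0.8 | 0.18 | 26% | 12% |

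**Sensitivity.** Widening the assumptions to 0.2 to 0.8 kg/m2 a year and SD 0.5 to 1.5, with 0.73 year, gives 9% to about 100% at follow-up at alpha 0.05 and 3% to about 100% at 0.0125. A middle case (0.4 a year, SD 0.75) gives 61% and 38%.

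**Between arms.** If both arms grow by the same expected amount g, the difference in mean change is (effect + g) − g = effect. Growth drops out in expectation. What remains is the age- and sex-related spread in the values, which widens the standard error.

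No calculation was made for MUAC, for which the article also gives no growth rate or SD. The reasoning is the same.

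**The case against.** The strongest reply is that the article is silent and nowhere says that raw values will be analysed. The unnamed chart may be a growth chart, both mentions of BMI cite a source that is not shown, and the full protocol or analysis plan could name the metric. That stands as far as it goes: a reader might infer that BMI and MUAC will certainly be analysed unstandardised, and the text does not support this. But plotting values on a chart does not define the variable that is tested, and the within-arm tests on nutritional status are stated outright.

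Three further replies limit the point.

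- **Between-arm bias.** A reader might infer that growth biases the comparison of arms. It does not, since shared growth cancels in expectation. A chance age difference between randomised arms is sampling error already covered by alpha. The article also uses the language of effectiveness only for the objective that includes the between-arm comparison.
- **Over-nourished participants.** Because no direction is stated, a reader might infer that opposite benefits in under- and over-nourished participants would cancel. The article gives no basis for this: its Introduction speaks of inadequate growth and underweight, and its Discussion of limited intakes. The dietary principle "A sufficient but moderate calorie intake" is general advice and does not show that overweight adolescents are to be enrolled. Only the request to state the direction survives.
- **Size.** The stricter post hoc level and the 12-week visit both give lower figures. This is correct. At 12 weeks the distortion is modest, but at follow-up 0.0125 does not remove it.

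**Conclusion.** The point holds for the within-arm analyses and should be addressed. The article makes BMI and MUAC primary outcomes in growing adolescents, specifies no age- and sex-standardised metric, and plans paired tests over about 9 months. If raw values are used, those tests cannot attribute a rise to the diet. On the assumed growth and variability, growth alone gives a significant within-arm BMI result at follow-up in about 30 to 99% of trials at alpha 0.05 and 14 to 96% at 0.0125, with a central case of 73% and 52%. At 12 weeks the ranges are about 7 to 26% and 2 to 12%, so the problem lies mainly at follow-up.

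These percentages illustrate the mechanism. The rates and SDs are not from the article, and wider assumptions widen the range. The between-arm comparison is not biased by growth; standardising there improves precision. The unstated direction of malnutrition is a matter for clarification.

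**What to change.** 1. Name one growth reference and analyse BMI-for-age and MUAC-for-age z-scores by sex. Where no reference applies, analyse the raw value with age and sex as covariates.
2. Adjust for the baseline value of the same measure.
3. Draw the nutrition conclusion only from the between-arm difference, and report within-arm changes as descriptive.
4. State which direction of malnutrition qualifies at entry, in the same metric, so that a rise has one meaning.

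The cost is small. The conversion needs only age, sex, BMI and MUAC; randomisation and the GARS-2 sample size are untouched. Fixing the metric before the data are analysed also removes a later choice between raw and standardised results. The small downside is reliance on an external growth reference.

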#### Intervention

The most effective practice paradigm for the care and treatment of ASD is inter-professional teamwork employing a multidisciplinary approach [19]. Therefore, in this research researchers try to include the professionals who commonly work with ASD as a nutritionist, physiotherapists (PT), occupational therapists (OT), and speech and language therapists (SLT).

*Protocol for SD+RT group*. This group will receive treatments as structured dietary interventions consulted and maintained by a nutritionist. Regular therapy will include physiotherapy, occupational therapy, and speech and language therapy. As a common approach for both groups, conventional care from the teachers, parents, and counselors for ASD will be continued. Treatment dosage will depend on age, ASD symptoms, and severity.

Physiotherapy interventions include balance training as Land-based & swimming-based exercises [20], gait training to improve gross motor function and coordination of autism [21], coordination practice [36], hippotherapy or therapeutic horse riding [22], gross motor function practice [23], proprioception training to improve motor functions & improving lower extremity strength [24], aerobic exercise training to improve sleep, motor skill and mood among ASD children [25], muscle strengthening to improve higher executive function [26].

An expert speech and language therapist will provide treatment based on ASD symptoms. Common treatment will include- Applied Behavior Analysis (ABA) [37], Applied behavior Consequence (ABC) [38], Relationship Development Intervention (RDI) [39], Cognitive Behavior Intervention (CBI), Social communication intervention (e.g Social Story) [40], Picture Exchange, Communication System (PECS), Augmentative and alternative communication (AAC), Visual schedule [41].

Occupational therapy intervention includes sensory integration that includes the 10 key therapeutic strategies [42] in the fidelity tool, on the individual needs of each child as, (a) setting up the space to encourage interaction, (b) providing for physical security, (c) offering options for sensory input, (d) achieving and preserving appropriate arousal levels, (e) modifying activities to offer the ideal challenge, (f) assuring the success of activities, (g) providing direction for behavior self-regulation, (h) establishing a fun atmosphere, (I) choosing an activity together, and (j) encouraging therapeutic partnerships [43]. These 10 areas will be divided into 3 primary categories as (i) modifying the environment and giving sensory possibilities for the kid throughout the therapy session; (ii) encouraging adaptive responses and offering the ideal challenge; and (iii) building the therapist-child relationship [44]. Other interventions include gross motor function through exercise including pegboard games, dexterity drills, crossword puzzles, ball games, balance training, sensory integration exercises, and play therapy [45]. Moreover, community mobility or travel training [46], cognitive behavioral therapy [47, 48].

A structured diet (SD) will be designed by a nutritionist. Participants will provide with written instructions about the healthy, gluten-free, casein-free, soy-free diet and vitamin and mineral supplement [13]. The nutritionist will provide detailed advice. The diet plan will depend on age, nutritional status, and BMI. Other comorbid diseases and allergies of the child and adolescent to specific foods and physical activity levels will consider. The major guiding principles of the dietary plans will include, (1) Consuming enough fruit and vegetables, especially leafy greens (preferably whole fruit), (2) A sufficient amount and quality of protein, (3) A sufficient but moderate calorie intake, (4) Consuming fewer "junk" meals and substituting them with wholesome snacks, (5) A wholesome, gluten-free, casein-free, and soy-free diet (HGCSF) that includes foods like poultry, fish, and meat as well as fruits and vegetables, potatoes, rice, and baby rice cereal, and (6) Refrain from using synthetic flavors, colors, and preservatives. Moreover, Vitamin or mineral supplements will be prescribed with the consent of a General Physician. The dosage will be determined by the physician.

*Protocol for UD+ RT group*. The group will receive Regular therapy as per the above protocol, but they will not receive any consultations from the nutritionist and will take the usual diet. After completion of the follow-up, they will be advised of the structured diet intervention based on the study result.

*Progression of interventions*. The intervention duration will be 12 weeks. 45 minutes of the session with the ASD Adolescents and their parents will be provided 3 times a week for each therapeutic intervention item. Participants will receive separate sessions for each therapy item (PT, OT, SLT, SD). The progression of interventions will be determined by subsequent professionals.

### Minimization of bias and blinding process

Assessors, patients, and therapists will be blinded to group allocation in this study. As this will be a multi-center trial of an organization, researchers plan to different assessors for each center. Randomization will be done by a person who is not involved in this research. The treatment providers will be blinded to the groups, but they will be aware of the treatment of their group, also participants will not be aware of the intervention of another group. The execution of the study will not involve the research team, and a separate assessor, treatment provider, monitoring team, and trial manager will be employed to guarantee trial coordination.

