### Study procedure

After the trial registration is obtained, researchers will start the phone call procedure to estimate the willing participants. As the primary screening of cases of “ASD with malnutrition” performed in the population-based survey, the parents will be directly contacted for participating in the trial. From the computer-based random serial, the first 70 ASD will be pooled for enrollment in the study. On the first day, an assessor blinded to group allocation will further screen and take a pre-test assessment. Then the participant will be treated in a multi-disciplinary approach with the consultation of a nutritionist, physiotherapist (PT), Occupational therapist (OT), and speech and language therapist (SLT). Both structured dietary treatment and regular therapy will be provided as three 45 minutes sessions per week for a total of 12 weeks. After 12 weeks, the post-test data will be obtained by the assessor. There will be a follow-up evaluation after 6 months of post-test. There will be a separate assessor for each of the treatment set-ups. The Consolidated Standards of Reporting Trials (CONSORT) manual will be followed when conducting the study. Fig 2 provides a summary of the study’s methodology.

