### Study setting

Both of the groups will receive treatment from two different centers of the Centre for the Rehabilitation of the Paralysed (CRP), the largest rehabilitation facility in Bangladesh. Specification of centers for therapy group allocation will not disclose, to ensure the physiotherapists and the patients are blinded to group allocation. Two study centers of an organization (one for control and one for experimental) were selected because of the availability of specialist multi-disciplinary team of physiotherapist, occupational therapist, speech and language therapist, child psychologist, educational psychologist, nutritionist and special educators were available altogether in that specialized organization.

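### Patients and therapists are called blinded although they know the treatment received, and one assessor per single-arm centre confounds any rater difference on GARS-2 with diet

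*Protocol article*

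**What the plan says.** The section on minimization of bias states: "Assessors, patients, and therapists will be blinded to group allocation in this study". The Abstract and the Study design section make the same three-way claim, and Study setting gives the means for two of the three groups: "Specification of centers for therapy group allocation will not disclose, to ensure the physiotherapists and the patients are blinded to group allocation".

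The bias section then qualifies the claim. Of providers it says: "The treatment providers will be blinded to the groups, but they will be aware of the treatment of their group". Of participants it promises only that they will not know the other group's intervention.

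Under Intervention, the structured-diet (SD) arm receives written instructions for a gluten-, casein- and soy-free diet, vitamin and mineral supplements, and separate diet sessions three times a week for 12 weeks. Of the usual-diet (UD) arm it says: "they will not receive any consultations from the nutritionist and will take the usual diet". No sham advice is described.

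On centres, Study setting says: "Two study centers of an organization (one for control and one for experimental) were selected". On assessors, Study procedure says: "There will be a separate assessor for each of the treatment set-ups". The bias section agrees: "researchers plan to different assessors for each center". Study procedure also describes the assessor as blinded to allocation.

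GARS-2, a 42-item behaviour rating scored 0–126, is a primary outcome and the one that sized the trial. Data analysis compares the groups at baseline, post-test and follow-up by MANOVA or a multivariate Kruskal-Wallis test. It names no baseline, assessor or centre term.

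**The concern.** Two things are at stake.

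The first is an accurate description of the trial. A family following a restrictive diet with supplements knows it is doing so, and the nutritionist who delivers the diet knows it too. Reporting these groups as blinded would understate the risk of bias for an outcome that depends on judgement.

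The second is attribution. If one assessor scores all SD participants and another scores all UD participants, a lenient or severe rater moves a whole arm. An observed GARS-2 difference then mixes the diet effect with the rater difference, and no analysis of these data alone can fully separate them. A larger sample does not help, because the number of assessors per arm stays the same.

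**Working it through.** **Who knows what**

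| Group | Stated | What the design gives them |
|---|---|---|
| Patients and families | Blinded | They know their own diet, supplements and nutritionist contact; only the other arm is withheld |
| Treatment providers | Blinded | Aware of the treatment of their own group, by the article's own words |
| Assessors | Blinded | No disclosure described; but each sees one arm only, and the safeguard in Study setting names physiotherapists and patients, not assessors |

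The first two rows contradict the claim. The third does not, but it leaves the claim fragile.

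**Confounding.** One arm per centre (Study setting) and separate assessors per centre (Study procedure; bias section) give arm = centre = assessor. An assessor term added to this layout would be collinear with arm.

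**The plan's own figure.** Inputs from Sample size: mean 4.7, SD 1.7 on the 0–10 scale, 25% improvement, 80% power, alpha 0.05, 1:1. Two-sided alpha is assumed.
- Design difference: 0.25 × 4.7 = 1.175.
- n per arm = 2 × (1.960 + 0.842)² × 1.7² / 1.175² = 32.9, rounded up to 33, so 66 in total. This matches the stated 66; the sizing is not at fault.
- With 35 per arm, power is 81.3% by the noncentral t (82.4% by the normal approximation).

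**What an offset would do.** Assumptions: no diet effect, post-test scores compared without baseline adjustment, a fixed difference b between the two assessors, SD 1.7, 35 per arm, two-sided 0.05. The values of b are chosen for illustration.
- SE = 1.7 × √(2/35) = 0.406.
- Rejection rate = probability that a t statistic with 68 df and noncentrality b/SE falls beyond ±1.995.
- Raw points = b × 12.6, assuming the 0–126 score converts linearly.

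| Offset b | In SD units | Raw GARS-2 points | Share of 1.175 | b/SE | False-positive rate |
|---|---|---|---|---|---|
| 0.17 | 0.10 | 2.1 | 14% | 0.42 | 7.0% |
| 0.3 | 0.18 | 3.8 | 26% | 0.74 | 11.3% |
| 0.5 | 0.29 | 6.3 | 43% | 1.23 | 22.8% |
| 0.75 | 0.44 | 9.5 | 64% | 1.85 | 44.4% |

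The offset can also work against the diet. With a true effect of 1.175 and an opposing offset of 0.5, the expected difference is 0.675 and power falls from 81.3% to 37.4%.

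**Under a change-from-baseline analysis.** If the same assessor scores a participant at both visits, b enters both scores and subtracts out. Two things do not: drift in a rater's standard between visits, and scoring influenced by knowing or guessing the arm. Neither can be sized from the documents.

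**The case against.** A reader might infer that assessors are unblinded by design. The documents do not support that. Study procedure says the assessor is blinded, the bias section keeps the research team out of the conduct of the trial, and a condensed article may leave masking procedures to the full protocol. What stands is narrower: the layout makes assessor blinding easy to break, and a single disclosure breaks it for the whole arm.

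A reader might also infer that a constant rater offset is certain to bias the main comparison. That goes too far. Data analysis is loosely worded, and the third study objective compares groups over pretest to post-treatment and pretest to follow-up, which can be read as comparing changes. The plan may intend an analysis in which the offset cancels. But no baseline term is named, and drift and expectation bias would remain on either reading.

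The offsets are assumed. The smallest one shown raises the error rate only to 7%, and the documents give no means of saying which row applies.

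BMI and mid-upper arm circumference, also primary outcomes, are less exposed to rater leniency. The article also partly discloses what it means by participant blinding, namely ignorance of the other arm. That explains the wording but does not make it correct: the opening sentence still claims more than the design provides.

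**Conclusion.** The concern holds in this form. The statement that patients and therapists are blinded is wrong as written: the article says "but they will be aware of the treatment of their group" of providers, and the diet arm cannot be unaware of its diet. Assessor blinding is asserted and not contradicted, but weakly protected.

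The confounding of assessor with arm is explicit and does not depend on whether assessors stay blind. Its size is unknown. The false-positive rates of about 7% to 44% are conditional on a post-test comparison without baseline adjustment, on assumed offsets of 0.17 to 0.75 and, for the raw-point equivalents, on linear conversion. They show sensitivity to rater differences and are not estimates of the bias in this trial.

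**What to change.** 1. In the Abstract, Study design, Study setting and the bias section, replace the blinding claim for patients and therapists with a statement that participants, families and treatment providers are not blinded to the treatment received. Claim assessor blinding only if assessors are kept from diet sessions, diet records and the centre-to-arm link, and say how. Cost: wording, and separating assessments from diet delivery.

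2. For assessments still to be done, have the two planned assessors each score about half of each arm, with the same assessor for a participant throughout where possible. Include assessor and baseline GARS-2 in the between-group model. Cost: travel between two centres of one organisation, with no extra staff. Because the assessors would then see both centres, the masking in step 1 matters more.

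3. Recruitment had already started when the article appeared. For participants already scored by one assessor per arm the rota comes too late: use a baseline-adjusted analysis and report the rater confounding as a limitation.

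4. None of this separates centre from arm. While each centre runs one arm, state that confounding as a limitation in the conclusions.
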